## Discussion

Our main goal for this study is to strengthen the scientific basis for understanding idiopathic haematopoietic neoplasms in children. By presenting the protocol before undertaking the actual analyses, we intend to improve the quality, integrity and transparency of the study.

Strengths of the first objective include the unselected national cohort, the prospective design and the register-based measure of outcome. This explorative study takes advantage of the iTFA elimination policy implemented in Denmark almost fifteen years ago, and nests this “societal experiment” in a setting where the effect of conditions from conception (and before) for development of certain diseases can be followed among individuals from birth and onwards. The study is possible due to complete identification of every resident in Denmark via a civil registration number. This number can be linked, on an individual level, to Danish birth, patient and medical registries; social and ethnic registries; and clinical and other national databases. The comprehensive linkage of datasets for both aims makes it possible to study mediation, confounding and/or modification of effects of iTFA for childhood haematopoietic neoplasms.

For the first objective we do not collect any individual data on iTFA intake. In contrast, all individuals are unselected in relation to iTFA exposure and later disease occurrence. This may be considered a very strong feature of the present study, as neither confounding from external or internal factors, nor the lack of individual data on iTFA intake, is a prerequisite for the study, as the influences of lifestyle differences (e.g. use of infant formula, individual diet intake, use of supplements), or biological (adipose tissue stores, weight changes during pregnancy and post-partum) which we would not be able to adjust for, are all independent of the iTFA legislation.

Nevertheless, the proposed study design, especially in the first objective, also implies some uncertainties, including a potential ecological fallacy. The exposure measure is applied equally to all members of the cohort before and after the ban, while the individual exposures have probably differed. However, a previous study has shown a marked decline of average iTFA intake resulting in elimination after the ban [32]. In the case-control study we investigate TFA exposure individually in all cases from 1988 to 2008. The variations in the exposure observed in the case-control study will then inform our assumptions taken in the cohort study.

Any societal changes preceding 1988 or succeeding 2008 will influence the exposed and control groups similarly, while results will be confounded by any potential societal changes occurring around the time where the trans-fat ban was implemented (e.g. 2003/04). However, we are unaware of such changes except for a screening for DS which we have taken into account by excluding children with DS.

Potentially exposure to TFA from maternal adipose stores could affect the “unexposed” group (born after the ban of iTFA) and postnatal influences like maternal feeding practice and weight gain, may also influence cancer risk through a non-TFA mechanism. Although this may indeed seem a possible limitation, since literature has shown that weight loss of the mother (e.g. during lactation) liberates TFA fat deposits [44], proper randomization in our societal experiment study is mimicked by separating exposed and non-exposed individuals by one point in time with a minimum of selection bias. Thus, it is an obvious strength to the present research design, that the individuals will be unselected, and generally representative of the Danish population, in relation to exposed vs. non-exposed to the trans-fat legislation, as well as to the development of haematopoietic neoplasms. However, since we do not know the exact mechanism between TFA and childhood neoplasms, we cannot account for a residual confounding which might affect observed associations. Residual confounding could be caused by additional components in food products with high contents of TFA. We are not able to investigate TFA levels at specific developmental stages during gestation, but since no knowledge exist on specific target windows for childhood cancers, this may not be relevant.

Other health outcomes in children, which will not be described in this protocol, will be investigated in future studies using the same study designs, include: negative birth outcomes, cognitive function, epilepsy, asthma, heart disease, eye diseases, bone fracture, and metabolic diseases like type 1 diabetes and childhood obesity.

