### Study population

The cancer registry is complete until December 31st 2015. To secure equal time of follow-up for cancer diagnosis in all individuals we censor at 7 years of age, which is the longest follow-up time in which we have information on possible cancer outcomes for all individuals.

We will exclude all children born with a Down’s Syndrome (DS) diagnoses due to their increased risk of childhood leukemia [35] and due to secular trends in DS incidence, because of a new screening practice for DS and other chromosomal aberrations introduced in 2004.

*In the first objective,* national birth cohorts of individuals born between January 1st, 1988 and December 31st, 2008 in Denmark will be included (Fig. 1). This is a register based study using the Danish civil registration number which will be linked to the Danish National Cancer Register, where the cancer patients are followed-up until December 31st, 2015.

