**Fig. 1 Fig1:**

Constitution of the exposed versus non-exposed groups of cases who developed haematological malignancy before the age of 7 years and registered in The Danish Cancer Registry (Objective 1)

The incidence of childhood haematopoietic neoplasms among 1,101,055 individuals from the period before the iTFA legislation born between January 1st, 1988 and August 31st, 2004, will be compared to the incidence of childhood haematopoietic neoplasms among 276,422 individuals from the period after the iTFA legislations born between September 1st, 2004 and December 31st, 2008, as a proxy of iTFA gestationally exposed or not exposed, respecitvely. In this overall time period approximately 740 incident haematopoietic neoplasms cases occurred in children before the age of 7 years.

*The second objective* is a case-control study investigating biomarkers of neonatal trans-fatty acid concentrations from stored DBS [34] from individuals who developed childhood haematopoietic neoplasms before the age of 7 years and born in the period 1988–2008 compared to matched controls (Fig. 2).

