### Statistical analysis

In objective 1 we will use a Cox proportional hazard model with age as the underlying timescale to investigate the hazard of childhood haematopoietic neoplasms in children born before and after the iTFA ban, as a proxy for iTFA exposed or not exposed in fetal life. Observations will be censored in case of death, immigration or at 7 years of age. To take the potential secular trend in the incidence of haematopoietic neoplasms into account we will model the variation in cancer risk across birth cohorts by a piecewise linear spline with a knot at 1st of September 2004. Further, we will investigate incidence trends over time.

By examining *all* children from the entire national birth cohorts it is reasonable to assume that all confounding variables will be equally distributed among the exposed and non-exposed individuals, but still we will investigate potential influence of secular variation or possible confounding effects which might have changed during the time period and which might be associated with both TFA exposure and haematopoietic neoplasms. Such potential confounders could be age of the mother at the time of giving birth, assuming accumulation of TFA with age and an older age for first time pregnancies over time. The median gestational age might have increased during the investigated time period, which would increase the average intrauterine exposure to TFA over the study period [44]. Smoking status during pregnancy might have decreased over time and smoking might be associated with increased cancer risk, smoking is also associated with gestational age and thereby with the length of the TFA exposure during pregnancy.

As sub-analysis we will exclude cancer cases diagnosed before the 90 day of life since the origin most likely is due to chromosomal alterations leading to oncogene activation [37]. If feasible we will investigate the first born only since some studies have shown higher risk of childhood cancers in the first born compared to their younger siblings [45] and sensitivity analysis of sub-types of haematopoietic neoplasms (leukemia and lymphoma). Further, we will investigate children with early diagnosis, e.g. before age 4 years.

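### Changes after 2008 do not affect both groups alike: about 3% of pre-ban but 69% of post-ban person-time falls after 2008, and the cohort model has no calendar-period term

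*Protocol article*

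**What the plan says.** Objective 1 compares "individuals from the period before the iTFA legislation born between January 1st, 1988 and August 31st, 2004" (1,101,055 children) with "individuals from the period after the iTFA legislations born between September 1st, 2004 and December 31st, 2008" (276,422 children); both figures stand with Fig. 1. On follow-up, the Study population section states "The cancer registry is complete until December 31st 2015" and "To secure equal time of follow-up for cancer diagnosis in all individuals we censor at 7 years of age".

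The Statistical analysis section plans a Cox model with age as timescale. The secular trend is handled by a piecewise linear spline in birth date, with its knot on the date that divides the groups. No calendar-time term is named. The section also says that "it is reasonable to assume that all confounding variables will be equally distributed among the exposed and non-exposed individuals", and then undertakes to look at secular variation all the same.

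The Discussion claims "Any societal changes preceding 1988 or succeeding 2008 will influence the exposed and control groups similarly". It concedes that changes around 2003/04 would confound the result, but adds "we are unaware of such changes except for a screening for DS which we have taken into account by excluding children with DS". The Study population section describes that screening more widely; Down's syndrome (DS) is excluded in part "because of a new screening practice for DS and other chromosomal aberrations introduced in 2004".

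**The concern.** The births end in 2008 but the follow-up does not. Cancer is counted up to age 7, so the outcome is still being observed in 2009–2015, and the children observed then are nearly all post-ban. A change in those years in diagnosis, coding, registration or postnatal exposure would reach one group and largely miss the other.

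The Discussion presents the ban as a societal experiment that mimics randomisation. The claim that later changes cancel out is one support for that reading. If it fails, a rise in recorded incidence after 2008 could hide a benefit of the ban and a fall could imitate one, and a reader who relied on the sentence would not look for either.

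**Working it through.** **Dates.** The last birth is 31 December 2008. Adding 7 years gives 31 December 2015, the registry end, so the protocol's 7-year limit reproduces. Pre-ban follow-up ends between January 1995 and August 2011, and post-ban follow-up between September 2011 and December 2015.

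**Person-time after 2008.** Assume births uniform within each group and no death or migration. A child born at calendar time b (2002 or later) is followed after 1 January 2009 for (b + 7) − 2009 = b − 2002 years.

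- Pre-ban births run from 1988.00 to 2004.67. Only those from 2002.00 on contribute: 2.67/16.67 = 16% of children, with a mean of 2.67/2 = 1.33 years. Group mean: 0.16 × 1.33 = 0.21 years; 0.21/7 = 3.0%.
- Post-ban births run from 2004.67 to 2009.00. All contribute, from 2.67 to 7 years. Group mean: (2.67 + 7)/2 = 4.83 years; 4.83/7 = 69.0%.
- Person-years after 2008: pre-ban 1,101,055 × 0.213 ≈ 0.23 million, all at ages above about 4.3 years; post-ban 276,422 × 4.83 ≈ 1.34 million, at all ages. The post-ban group is 276,422/1,377,477 = 20% of the cohort but holds 1.34/(1.34 + 0.23) = 85% of this person-time.

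With the boundary in the Hypotheses section (born 1988–2003 against 2004–2008) the shares are 1.8% and 64.3%, so the conclusion does not depend on the boundary.

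**Effect on the contrast.** Suppose the ban has no effect and incidence is multiplied by f from 2009 on; f is an assumption. With a constant hazard over ages 0–7 and no trend term, the pre/post rate ratio is

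(0.970 + 0.030 f) / (0.310 + 0.690 f).

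For f = 1.10 this is 1.003/1.069 = 0.94; for f = 1.20, 1.006/1.138 = 0.88; for f = 0.80, 0.994/0.862 = 1.15.

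The protocol plans a birth-cohort spline, and does not say whether a step at the cut is fitted with it. Poisson models on a birth-month by age grid (740 events, uniform births, constant hazard, age categories) give:

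| Model | Rise of 10% | Rise of 20% |
|---|---|---|
| Step only: pre/post HR | 0.94 | 0.88 |
| Step and one linear cohort trend: pre/post HR | 0.95 | 0.91 |
| Step and slope change at the knot: pre/post HR | 0.97 | 0.95 |
| Continuous spline, no step: slope change per birth year | +1.9% | +3.7% |

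The step with a slope change has a standard error of about 0.18 on the log scale, so the shifts are ln 0.97 = −0.030 and ln 0.95 = −0.051, about 0.2 and 0.3 standard errors. In that model the slope takes up the rest, about 2.3% per birth year for the 20% rise. For the continuous spline the slope change has a standard error of about 4.5%, so the shifts are 1.9/4.5 ≈ 0.4 and 3.7/4.5 ≈ 0.8 standard errors.

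**The case against.** The sentence has a sound narrow reading. Objective 1 concerns fetal exposure, and every child was born by the end of 2008, so later changes in prenatal exposure cannot touch either group. But the sentence speaks of changes of any kind, and the same Discussion lists postnatal influences on cancer risk. The narrow reading is what the text should say, not what it says.

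The planned spline gives some protection. Children born just before and just after the cut share nearly the same calendar follow-up, and the post-knot slope takes up part of a later period effect. This stands, and is why 0.94 and 0.88 must not be read as the bias of the planned model. They belong to a comparison without any trend term.

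The protocol is also not blind to secular change. It promises to examine secular variation and incidence trends over time, admits confounding around 2003/04, and mentions residual confounding. These are fair points, but an incidence trend that is only examined does not adjust the contrast, and none of them withdraws the claim about changes after 2008.

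A reader might infer that screening for other chromosomal aberrations is an uncontrolled confounder. The document does not support this: it states a raised leukaemia risk for DS only and gives none for the other aberrations. What remains is a difference in scope between two sections.

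**Conclusion.** The claim about changes after 2008 is incorrect as worded, and the planned model has no term that would restore it. The person-time split (3% against 69%) follows from the protocol's dates and needs only roughly even births within groups.

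The possible bias is modest under the planned spline: a pre/post hazard ratio of about 0.97 or 0.95 for an assumed 10% or 20% rise if a step is fitted, or a slope change of 1.9% or 3.7% per birth year if it is not. These sizes rest on assumed period changes and a flat age-specific hazard; with an assumed hazard peak at ages 2–5 the step figures are 0.97 and 0.945.

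It would be tempting to conclude that the comparison is biased. The protocol reports no change in diagnosis, coding or registration in 2009–2015, so only susceptibility is shown. Objective 2 matches controls on date of birth and is largely unaffected.

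**What to change.** 1. Limit the Discussion sentence, for the years after 2008, to prenatal exposures, and state that other changes in 2009–2015 fall mainly on post-ban births.

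2. Add a sensitivity analysis that splits follow-up by calendar time and includes a smooth calendar-period term. Because calendar time equals birth date plus age, a linear period trend cannot be told apart from a linear cohort trend on the age timescale. The period spline should therefore carry that trend, with the contrast at the cut kept.

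3. State the precision of this analysis. With a 3–5 df period spline the standard error of the step is about 0.16–0.17, or more if the slope change at the knot is also kept. A bare step has 1/√(740 × 0.20 × 0.80) ≈ 0.09. At 0.165, 80% power is reached only at a hazard ratio of about exp(2.80 × 0.165) ≈ 1.6. The analysis shows whether the estimate is stable; it cannot resolve a bias of 3–5%. Placebo cut dates within the pre-ban births would not substitute for it, since they do not test a change after 2008.

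4. Minor: make the Study population section and the Discussion agree on what the 2004 screening covered. Excluding children with other registered chromosomal aberrations can be an optional sensitivity analysis, bearing in mind that detection of these diagnoses may itself have changed over time.

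The cost is a wording change and a few model runs on data already to be linked. The protocol already provides for updates.

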### Power calculation

Using the command stpower for the log-rank test for comparison of two survival functions in Stata 14 we calculated the least detectable hazard ratio (exposed versus unexposed) to be 1.35 assuming 80% power and a significance level of 5% in objective 1 (the cohort study) [42].

In objective 2 (the case-control study) we have a sample size of 700 cancer cases and 700 controls, and assuming 80% power, the least detectable OR will be between 1.35 and 1.75, depending on the exposure among the controls (10–90%). The power analysis for the matched 1:1 case-control study was performed using the power mcc command in Stata 14 [43].

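### The protocol's single-cut-date argument does not answer possible carry-over of stored maternal TFA into the post-ban group, which would pull the before/after hazard ratio toward 1

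*Protocol article*

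**What the plan says.** Objective 1 compares the incidence of haematopoietic neoplasms before age 7 "among 1,101,055 individuals from the period before the iTFA legislation born between January 1st, 1988 and August 31st, 2004" with that "among 276,422 individuals from the period after the iTFA legislations born between September 1st, 2004 and December 31st, 2008". Birth before or after the cut stands in for fetal iTFA exposure or its absence (Study population; Statistical analysis). According to the Background, the order took effect on 31 March 2003 with a transition period to 1 January 2004, so the cut falls eight months after full effect.

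Three statements bear on stored TFA:

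- Statistical analysis treats maternal age as a possible confounder, "assuming accumulation of TFA with age".
- The Discussion, in the paragraph on not collecting individual intake data, names adipose stores among lifestyle and biological influences that cannot be adjusted for but "are all independent of the iTFA legislation".
- Two paragraphs later: "Potentially exposure to TFA from maternal adipose stores could affect the" group labelled unexposed. The paragraph notes that maternal weight loss releases such deposits, calls this a possible limitation, and replies that "proper randomization in our societal experiment study is mimicked by separating exposed and non-exposed individuals by one point in time".

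Study population says iTFA in dried blood spots (DBS) will help to validate the effect of the elimination. The Discussion says exposure variation in the case-control study will inform the cohort assumptions.

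**The concern.** The reply does not meet the problem it answers. A clean cut in calendar time, with no selection around it, makes the groups comparable in composition. It does not make the exposure label correct: even a perfectly randomised comparison is diluted if the control arm receives some of the exposure. The protocol's own premises (accumulation with age, later release) are those under which dilution could occur, and the eight-month lag roughly covers dietary intake during a pregnancy but not fat stored before it.

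The statement on independence sits badly with this. How much fat a mother carries may be unrelated to the law, but how much TFA that fat contains depends on what she ate before the ban and how long ago.

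At stake is the reading of a null or weak objective 1 result. As written, the reader is told that carry-over has been dealt with by design, when it remains a competing explanation.

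**Working it through.** **Inputs from the protocol.** Pre-ban births 1,101,055; post-ban births 276,422 (276,422 / 1,377,477 = 20.07%); about 740 cases; post-ban window of 52 months. Power calculation, for 80% power at the 5% level: "we calculated the least detectable hazard ratio (exposed versus unexposed) to be 1.35".

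**The plan's own figure.** Two-sided 5% is assumed (z-sum 1.960 + 0.842 = 2.802).
- Schoenfeld, 740 events: exp(2.802 / √(740 × 0.2007 × 0.7993)) = 1.29. Freedman with unequal allocation: 1.32.
- With 700 events: 1.30 and 1.34.

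None gives exactly 1.35; the stated figure is slightly conservative, and the point does not rest on the difference. By Schoenfeld, 740 events give 90% power at HR 1.35.

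**Dilution, simple form.** If a fraction f of the excess risk persists after the cut, HR_obs = HR / (1 + f(HR − 1)). The documents give no f, so a range is shown for a true HR of 1.35:

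| f | HR_obs | Power, 740 events |
|---|---|---|
| 0 | 1.35 | 90% |
| 10% | 1.30 | 83% |
| 20% | 1.26 | 72% |
| 30% | 1.22 | 59% |
| 50% | 1.15 | 33% |

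**Dilution that fades.** Assumptions: stores supply a share s of fetal iTFA on 1 January 2004 and decay with half-life h; births are even over months; log risk is linear in exposure. Mean residual exposure r is the average of s × 0.5^((birth date − 2004)/h), and the expected two-group HR is 1.35^(1 − r):

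| s, h | r, all post-ban | HR | r, from Sept 2006 | HR |
|---|---|---|---|---|
| 25%, 1 y | 0.050 | 1.33 | 0.020 | 1.34 |
| 25%, 2 y | 0.103 | 1.31 | 0.068 | 1.32 |
| 50%, 1 y | 0.100 | 1.31 | 0.039 | 1.33 |
| 50%, 2 y | 0.205 | 1.27 | 0.136 | 1.30 |

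Before rounding, the later start moves the HR by 0.012 to 0.027. Poisson fits to the expected counts with a before/after step and a common linear trend also give 1.27 to 1.33. In a continuous spline with no step, the change in log-rate slope at the knot is −0.083 per year without carry-over and −0.074 to −0.083 with it, against a standard error (SE) of about 0.05, so it hardly moves.

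**Cost of a start in September 2006.** This drops 24 of 52 months: 276,422 × 24/52 ≈ 127,600 births (46%). At a true HR of 1.35 without carry-over:
- Post-ban cases: 740 × 276,422 / (1.35 × 1,101,055 + 276,422) = 116; pre-ban cases 624.
- Remaining post-ban cases: 116 × 28/52 ≈ 62.5, or 63 to 64 with the carry-over above.
- SE of log HR: √(1/624 + 1/116) = 0.10, rising to √(1/624 + 1/62.5) = 0.13. With a common linear trend it rises from 0.13 to 0.16.
- Least detectable HR (Schoenfeld, events spread evenly over births): 1.29 rises to 1.40.

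**The case against.** - **A check exists.** A reader might infer that the plan has no check on carry-over. It does not go that far: DBS iTFA is measured in cases born throughout 1988 to 2008 and is meant to inform the cohort assumptions. This stands. What is missing is any stated link from those measurements to the objective 1 groups.
- **The independence statement is not the dismissal.** It belongs to a paragraph on influences that cannot be adjusted for, and can be read as differences between mothers in fat mass. That is a fair reading, so this is a matter of reconciling two paragraphs. The dismissal itself rests on the randomisation analogy.
- **Carry-over is only possible.** The protocol words it as a possibility, and its example of weight loss is lactation, which is postnatal. This stands: the direction of bias is clear only if carry-over occurs, and its size is unknown. Starting the decay at 31 March 2003 would multiply the residuals by 0.59 to 0.77.
- **For the effect of the law, residual stores are part of the effect.** Hypotheses and objectives speaks of reduced iTFA, not none. This is correct for the policy question. Misclassification arises when the contrast is read as a proxy for fetal exposure, which the protocol also does.
- **The protocol already guards against over-reading a null.** Methods says a null in objective 1 need not imply one in objective 2. That helps, but it does not name carry-over as a reason.
- **An article may leave sensitivity analyses to a fuller document.** Agreed; the absence alone would be no finding. The point is that the article raises the problem and closes it with an argument that does not apply.

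**Conclusion.** The point holds as a flaw of argument with a modest analytic consequence. The randomisation analogy addresses selection, not misclassification, and the two Discussion paragraphs on adipose stores need reconciling. If carry-over exists, the before/after HR is attenuated: a true 1.35 becomes 1.27 to 1.33 under the fading scenarios, or 1.26 with power down from 90% to 72% if 20% of the excess risk persists. All these sizes rest on assumed carry-over; the documents supply none.

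A reader might also infer that trend adjustment makes the dilution much worse, because residual exposure is greatest just after the cut. That needs a model with both a step and a slope change at the cut (1.21 to 1.30 under the same assumptions). Statistical analysis specifies a piecewise linear spline with a knot and states no step. With a step and a common trend the dilution matches the unadjusted figure, and in a continuous spline the slope change barely moves. The stronger claim is therefore not supported.

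**What to change.** 1. In the Discussion paragraph on maternal stores, replace the randomisation argument with a statement that carry-over, if present, biases the before/after contrast toward the null, so that a null in objective 1 is not evidence of no fetal iTFA effect.
2. In the earlier paragraph, remove adipose stores, as a source of TFA, from the influences called independent of the legislation.
3. Pre-specify one sensitivity analysis that omits or grades births soon after 1 September 2004, for example with unexposed births from September 2006. Let DBS iTFA by birth year inform the window, which gives the stated feedback from objective 2 a concrete use.

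The cost is two wording changes and one further run on data already held. The loss of precision is real: about 63 post-ban cases remain if the true HR is 1.35, and in the worst fading scenario the expected z falls from 2.4 (log 1.269 / 0.099) to 2.0 (log 1.296 / 0.131) although the HR moves toward its true value. The run should therefore be labelled a sensitivity analysis, should not replace the main contrast, and should not be presented as able to tell carry-over from a true null.
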